### Primary outcome

Since the objective of this study is to investigate the efficacy of SAEM-CS on motor function recovery in patients with cerebral infarction, the primary outcome will be assessed via changes on the Fugl‐Meyer Assessment (FMA) scale for motor function. The FMA is widely used as a qualitative measure of motor function and is used in the current study to assess upper and lower limb function. The FMA is categorized into 50 items based on a six-stage recovery process of Brunnstrom’s hemiplegia classification and progress record. This assessment is an ordinal scale, in which 0 is given for unable to perform, 1 for partial performance, and 2 for complete performance. The FMA has a possible total score of 100, 66 points of which apply to the upper limbs and 34 points to the lower limbs [16].

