### Sample size

The sample size was calculated based on Cohen’s formula. As there are very few precedent studies that have conducted SAEM-CS similar to the present study, and because characteristics of the variables being tested are diverse, it was difficult to select and apply a single effect size. Thus, we set the effect size as 0.25 based on a medium *f*, which is one of Cohen’s criteria [32]. Accordingly, we have established the number of groups as 4, number of repetitions as 3, effect size as 0.25, significance level as 0.05, and statistical power as 0.8. Therefore, the total sample size required for a repeated measures ANOVA (taking into account interaction time with the treatment method), calculated using G*power, is 40 (10/group) [33].

Also, because the present study is an exploratory clinical trial, we determined that a total of 60 participants, 15 in each group, would be more appropriate. We based this on a previous study that recommended 12 participants per group for pilot studies that lack prior information [34] and other conditions used to determine the sample size for a pilot study [35] that gave a sample size of 12 per group, to which a drop-out rate of 25 % was applied. In order to minimize the dropout, the CRC will manage the treatment schedule of subjects.

Moreover, we considered the feasibility of the study, since participants will be patients with CI (which, as of 2014 average 46 per month) being treated at the Department of Neurology at the Chonnam National University Hospital. Considering the fact that among them, only 10–20 % will receive inpatient treatment at the Department of Rehabilitative Medicine and meet the selection criteria, it reaffirmed our estimation that 60 participants would be appropriate and feasible to achieve the study objectives. This also takes into account recruitment, study period, and drop-out possibilities.

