### Data analysis

Continuous data will be presented as means and standard deviations, while categorical data will be presented as frequencies and percentages. A repeated measures ANOVA will be conducted for the FMA and all secondary outcomes (NIHSS, MBI, FIM, K-MMSE, 9HPT, ASHA-NOMS, FAC, EQ-5D, MAS, Hand Grip Strength, and MEPs). Dependent variables include measured values before and after intervention and the measured values 4 weeks after completion of intervention. An *F* test will be conducted to detect differences between therapies, and Tukey’s post hoc test will be conducted to identify the groups. Repeated contrast tests will be conducted to account for time differences in each group, and the interaction group and time test will be conducted. A *p* value of <0.05 will be considered significant, and participants who drop out of the study will be excluded from the analysis. In brief, only complete case analyses will be used; thus, only subjects who complete the three evaluations will be analyzed. All statistical analyses will be performed using SPSS version 22.0 software (SPSS Inc., Chicago, IL, USA).

Data from participants who engage in less than 70 % of protocol adherence (i.e., receive <10 treatments from 15 trials) will be eliminated. Missing values will be implemented by multiple imputations. In addition, statistical differences will be verified by comparing attribution between eliminated and completed participants to check particular factors causing drop-out.

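### The step that names the better arm (therapy F test, then Tukey) averages pre-treatment FMA into the comparison, while the group-by-time test that was powered has no arm-level comparison tied to it

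*Protocol article*

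**What the plan says.** Three sections of the protocol article bear on this.

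- **Primary outcome:** "the primary outcome will be assessed via changes on the" FMA. The endpoint is change, not level.
- **Sample size:** the calculation is for a repeated measures ANOVA, "taking into account interaction time with the treatment method". The power figure therefore belongs to the group-by-time interaction.
- **Data analysis:** "Dependent variables include measured values before and after intervention and the measured values 4 weeks after completion of intervention". Pre-treatment FMA is thus one of three outcome values. An F test looks for differences between therapies, and Tukey's "post hoc test will be conducted to identify the groups". The interaction test appears in the following sentence, after the repeated contrasts over time, with no post hoc comparison attached.

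The Randomization section adds that baseline is measured before allocation.

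**The concern.** In a repeated measures ANOVA, the between-subject therapy factor, and a Tukey test on that factor, compare arm means taken over all repeated values. Here one of the three values predates treatment, and at that visit the arms can differ only by chance. Three things follow:

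- A treatment effect that is the same at both later visits is diluted to two thirds.
- Stable between-patient differences in severity stay in the error term, although the baseline measurement could remove much of them.
- Chance imbalance in baseline FMA, likely enough at 15 per arm, carries into the comparison of therapies.

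The Objective is to compare SAEM-CS with each of the other approaches, so the arm-level step is the one that answers the question. As written, the endpoint is change, the power is for differential change, and the arm comparison is of visit-averaged level. A real benefit could show as a significant interaction beside a null Tukey result, with nothing in the text to say which governs.

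**Working it through.** **Inputs from the Sample size section.** There are four arms, and the design values are "number of repetitions as 3, effect size as 0.25" (Cohen's f). Alpha is 0.05 and the power target is 0.80. Calculated N is 40; planned N is 60. The drop-out rate is 25%, and the Data analysis section keeps only patients with all three evaluations. That leaves 60 × 0.75 = 45 patients, or 4 × 12 = 48 if the pilot figure of 12 per group is what remains. The correlation ρ between visits is not stated. I assume 0.5, equal between all visits, with sphericity.

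**Step 1: reproduce the stated figure.** For the interaction, λ = f²·N·m/(1 − ρ), with df (k − 1)(m − 1) = 6 and (N − 4)(m − 1). At N = 40, λ = 0.0625 × 40 × 3/0.5 = 15 with df 6 and 72, which gives power 0.805. At N = 36 power is 0.749, so 40 is the smallest balanced N that reaches 0.80. Other correlations do not give 40: ρ = 0 needs 76, ρ = 0.3 needs 56 and ρ = 0.7 needs 28.

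**Step 2: put the same effect on the therapy factor.** Take arm effects that are zero at baseline and equal at both later visits, with variance v between arms in SD² units. Over the visit pattern (0, 1, 1) the mean is 2/3 and the variance 2/9. Then:

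- interaction f² = v × 2/9 = 0.0625, so v = 0.28125
- therapy-factor f² = v × (2/3)² = 0.125, so f = 0.354

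For the therapy F test, λ = 0.125·N·3/(1 + 2ρ), with df 3 and N − 4. At ρ = 0.5 this is 0.1875·N.

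| Patients analysed | λ, therapy F | Power, therapy F | Power, interaction |
|---|---|---|---|
| 40 | 7.50 | 0.57 | 0.81 |
| 45 | 8.44 | 0.63 | 0.86 |
| 48 | 9.00 | 0.67 | 0.89 |
| 60 | 11.25 | 0.78 | 0.95 |

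The therapy F test needs 64 completers for 0.80.

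**Step 3: sensitivity to ρ, with f held at 0.25.** At 60 analysed, the therapy F test has 0.87 (ρ = 0.3), 0.83 (0.4), 0.78 (0.5) and 0.66 (0.8). At 45 to 48 it stays below 0.80 at every ρ examined from 0.3 to 0.9. At ρ = 0.3 it is no worse than the interaction (0.87 against 0.85 at 60), but that ρ does not reproduce N = 40.

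**Step 4: the Tukey step.** I simulated SAEM-CS against control with 8,000 runs, ρ = 0.5 and effects scaled to interaction f = 0.25. If only SAEM-CS differs, v = 3d²/16, so d² = 1.5 and d = 1.22 SD. If SA and rTMS have half its effect, v = d²/8, so d² = 2.25 and d = 1.5 SD.

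| Per arm | Pattern | Tukey on three-visit mean | Tukey on week-3 FMA adjusted for baseline |
|---|---|---|---|
| 15 | SAEM-CS only | 0.53 | 0.88 |
| 15 | SA, rTMS half | 0.76 | 0.98 |
| 12 | SAEM-CS only | 0.43 | 0.78 |
| 12 | SA, rTMS half | 0.63 | 0.93 |

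Tukey on week-3 change from baseline lies between the two: 0.75 and 0.93 at 15 per arm.

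**The case against.** The best defence is that the interaction test is planned. With baseline among the repeated values, that test is the test of differential change. It fits the endpoint and the sample size, and at ρ = 0.5 it has 0.86 or more with 45 completers. Entering baseline as a repeated measure is therefore not an error in itself. This stands. What it does not supply is the arm comparison: the interaction is a 6-df omnibus test, and the only step written to separate arms hangs on the therapy factor.

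A reader might infer that the protocol claims 80% power for the therapy F test or for Tukey. It does not: the Sample size section ties that figure to the interaction.

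A reader might also put f = 0.25 directly on the three-visit mean and find power of 0.31 at N = 40 and 0.46 at N = 60, with about 124 patients needed. Those numbers are arithmetically right but describe a different and smaller treatment effect from the one the plan powered, so they overstate the loss.

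The trial calls itself a pilot and exploratory, and its final N rests on pilot guidance plus drop-out rather than on the power calculation. That lowers the severity without removing the point. A separate analysis plan could add detail, but the article already fixes the dependent values, the F test and the post hoc test, so such a plan would have to depart from it.

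**Conclusion.** The point holds in a limited form. The arm-identifying step tests a visit-averaged level that includes baseline, while the endpoint and the sample size concern change. At the plan's own effect size and ρ = 0.5, this costs about 0.22 in power at 45 to 48 completers (0.63 to 0.67 against 0.86 to 0.89) and 0.17 at 60 (0.78 against 0.95), relative to the interaction. For Tukey on SAEM-CS against control at 15 per arm, it means 0.53 to 0.76 where baseline adjustment would give 0.88 to 0.98.

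It is tempting to say that the plan would miss a real SAEM-CS benefit most of the time. The documents do not support that as a general statement. A 1 SD benefit with SA and rTMS at half does give Tukey power of only 36% at ρ = 0.5. But its interaction f is √(1/8 × 2/9) = 0.167, below the plan's 0.25. At the plan's f and 15 per arm, Tukey succeeds more often than not; it falls below one half only in the less favourable pattern at 12 per arm.

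The figures rest on an assumed correlation, sphericity and an effect that is constant after baseline. Severity: should-fix.

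**What to change.** In the Data analysis section:

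- Name the group-by-time interaction as the primary omnibus test for FMA.
- Base the Tukey-adjusted arm comparisons on post-baseline FMA with baseline FMA as a covariate, either by ANCOVA or by a mixed model of the two post-baseline visits. Comparing change from baseline is an acceptable simpler alternative. Do not use the visit-averaged group factor for this step.

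In the Sample size section, state that the 0.8 power applies to the interaction test only, and give the correlation assumed.

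The cost is wording. Baseline FMA is already collected, the named software fits these models, and neither the sample size nor the visit schedule changes.

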## Methods/design

### Objective

The objective of this study is to compare the efficacy of SAEM-CS on motor function recovery to physical therapy, rTMS, and SA. Further, we aim to explore the synergistic effect of converging SA and rTMS, which are known to be effective in promoting the recovery of motor function, in patients with CI.

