## Discussion

This protocol, following the Standard Protocol Items: Recommendations for Interventional Trials (SPIRIT) advice and Consolidated Standards Of Reporting Trials (CONSORT) 2010 guidelines, is designed to explore the synergistic effect of SAEM-CS on the recovery of motor function in patients in the acute stage of CI [36] (Additional file 4). We expect that rTMS will enhance the effect of SA and compensate for a commonly encountered problem in SA treatment: specifically, difficulty in twirling the acupuncture needle (as these needles should be twirled more than 200 times/min).

SAEM-CS is a treatment technique that combines LF-rTMS over the M1 region hot spot (motor cortex at the contralesional hemisphere) and SA stimulation of MS6 and MS7 at the upper limb regions of the lesional hemisphere to promote optimal functioning in patients following stoke. Despite other research showing that HF-rTMS applied to the lesional hemisphere more effectively improves motor function than LF-rTMS applied to the contralesional hemisphere in the early phases of stroke [9], LF-rTMS is selected for the combined SAEM-CS approach because there is some concern about complications that can arise due to the simultaneous use of SA and rTMS in the same hemisphere, and since we cannot completely exclude the interfering effects of HF-rTMS, even with non-magnetic needles. rTMS creates a powerful magnetic field near the stimulated area; therefore, all metal materials must be removed [37]. For rTMS and SA therapies that are conducted simultaneously (during SAEM-CS), we use a KOS-92 non-magnetic steel acupuncture needle that contains a much higher percentage of nitrogen (N) than STS304N1; thus, even in high processing volumes, the needle has no magnetic properties. The same method used in the SAEM-CS approach is employed for the SA and rTMS therapies. Thus, manual stimulation and electroacupuncture are not conducted in the SA group, and LF-rTMS is applied to the contralesional hemisphere in the rTMS group.

In the current study, we select patients hospitalized within 1 month after acute stroke in order to increase the homogeneity of the experimental population. This period was also chosen to increase reliability, because the most important period of recovery falls within the acute and subacute stages of ischemic stroke [38].

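### The plan's only arm-specific tests of change are within-group time contrasts, which cannot show that SAEM-CS beats another arm, and it does not say which test decides efficacy

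*Protocol article*

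**What the plan says.** The objective is comparative: to "compare the efficacy of SAEM-CS on motor function recovery to physical therapy, rTMS, and SA". The Primary outcome section defines the endpoint as change on the Fugl-Meyer Assessment (FMA).

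The Data analysis section specifies a repeated-measures ANOVA on the values at baseline, end of intervention and follow-up. It then lists these tests:

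- Between therapies, an overall F comparison: "test will be conducted to detect differences between therapies, and Tukey’s post hoc test will be conducted to identify the groups".
- Within each arm, over the visits: "Repeated contrast tests will be conducted to account for time differences in each group".
- In the same sentence, "and the interaction group and time test will be conducted".

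One threshold covers them all: a p "value of <0.05 will be considered significant". No test is named as the one that decides efficacy, and the within-group contrasts are not labelled descriptive.

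Two other parts of the protocol bear on how the contrasts can be read. The Inclusion criteria take patients within 1 month of infarction, and the Discussion supports that window partly because "the most important period of recovery falls within the acute and subacute stages of ischemic stroke". The Study design section gives conventional rehabilitation twice a day to every arm, control included.

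**The concern.** Improvement is expected in all four arms even if SA, rTMS and SAEM-CS add nothing. A significant change over time in one arm therefore shows that patients in early rehabilitation got better. It does not show that the added therapy helped, and it does not compare arms.

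This matters because of what the other tests leave open. A significant interaction says that the arms did not all follow the same course, but not which arm differed. Tukey names arms but, on the group factor, does not compare change. Someone asking which therapy improved the FMA more will find arm-by-arm tests of change only in the within-group contrasts. Two misreadings are then possible: taking recovery in the SAEM-CS arm as a treatment effect, or separating arms because one contrast reached p<0.05 and another did not.

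**Working it through.** **1. The plan's own figure.** The Sample size section uses "number of groups as 4, number of repetitions as 3, effect size as 0.25, significance level as 0.05, and statistical power as 0.8" for a "repeated measures ANOVA (taking into account interaction time with the treatment method", and obtains a total of 40. The between-visit correlation ρ and the sphericity factor are not stated; I assume 0.5 and 1.

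- Noncentrality: λ = f²·N·m/(1−ρ). At N = 40, λ = 0.0625 × 40 × 3/0.5 = 15.
- Degrees of freedom: (4−1)(3−1) = 6 and (40−4)(3−1) = 72.
- Power is 0.805 at N = 40 and 0.749 at N = 36, so 40 reproduces. At the planned N = 60, λ = 22.5 and power is 0.954.
- With ρ = 0, 0.3 or 0.7 the required N would be 76, 56 or 28.

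The test that the trial is sized on is thus the 6-df omnibus interaction.

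**2. What each planned test can answer.**

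| Test | Names the arms? | Compares change between arms? |
|---|---|---|
| Between-therapy F and Tukey, on the group factor | Yes (Tukey) | No: means averaged over three visits, baseline included |
| Group-by-time interaction | No | Yes, all four arms at once |
| Repeated contrasts in each group | One arm at a time | No: change without a comparator |

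Repeated contrasts compare adjacent visits: baseline with 3 weeks, then 3 weeks with follow-up. Change from baseline to follow-up is not one of them.

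**3. Within-arm contrasts when no treatment works.** Inputs: 15 per arm (Study design) and α = 0.05, taken as two-sided. Let d be mean change divided by the SD of change, equal in all arms. The protocol gives no value, so a range is shown. For a paired t test with 14 df, the critical value is 2.145 and the noncentrality is d√15. Let p be the chance that one arm is significant.

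| d | d√15 | p | SAEM-CS significant, control not: p(1−p) | All four significant: p⁴ | Arms disagree: 1−p⁴−(1−p)⁴ |
|---|---|---|---|---|---|
| 0.25 | 0.97 | 0.147 | 0.126 | <0.001 | 0.471 |
| 0.5 | 1.94 | 0.438 | 0.246 | 0.037 | 0.863 |
| 0.8 | 3.10 | 0.821 | 0.147 | 0.455 | 0.544 |
| 1.0 | 3.87 | 0.949 | 0.048 | 0.811 | 0.189 |
| 1.5 | 5.81 | >0.999 | <0.001 | 0.999 | 0.001 |

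Sensitivity of the SAEM-CS versus control column at d = 0.5, 0.8 and 1.0:

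- With 12 analysed per arm: 0.228, 0.204 and 0.103.
- With an error term pooled over arms (56 df, 15 per arm): about 0.24, 0.12 and 0.03.

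In 20,000 simulated trials per value of d, restricted to those where the between-group test of change was not significant, the arms still disagreed in 86%, 52% and 17% at d = 0.5, 0.8 and 1.0.

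**4. The between-arm test of change.** In the same simulations the F test on change between groups rejected in 5.0%, 4.8% and 4.9% of trials. Common recovery cancels.

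Tukey on change also suits the endpoint better than Tukey on averaged means. Assume SAEM-CS gains 0.8 SD at both later visits, the other arms gain nothing extra, and all visits are equally correlated.

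- Averaged means: the difference is (0 + 0.8 + 0.8)/3 = 0.533 and the SD is √((1+2ρ)/3), giving 0.533/0.816 = 0.65 at ρ = 0.5 and 0.533/0.931 = 0.57 at ρ = 0.8.
- Change from baseline to one later visit: the difference is 0.8 and the SD is √(2(1−ρ)), giving 0.8/1.000 = 0.80 and 0.8/0.632 = 1.26.
- Simulated power for SAEM-CS versus control, change against averaged means: about 33% against 21 to 22% at ρ = 0.5, and 78 to 79% against 15% at ρ = 0.8.

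**The case against.** The strongest reply is that the comparison asked for is already planned. The sentence with the within-group contrasts goes on to the group-by-time interaction, the sentence before it plans the F test and Tukey, and the trial is sized on the interaction. The contrasts also have a proper use: they describe the course of recovery and whether gains last after treatment ends. The trial calls itself a pilot and exploratory, and an analysis plan that is not shown might name the deciding test.

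Much of this stands. A reader might infer that the plan will judge efficacy from within-arm p values, or rank the arms by which of them are significant. The document says neither, and its objective and sample size point the other way. A reader might also infer that false separation of arms is likely whatever the recovery. It is not: it matters for small to moderate recovery and disappears when recovery is large, leaving only the risk that recovery in any arm is called efficacy. The percentages rest on assumed values of d and on how the contrast's error term is formed.

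What does not fall away is the gap in step 2. It concerns tests that the article itself lists, so it is not merely detail left to another document. None of the between-group tests, as usually run, says which arm changed more than which.

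**Conclusion.** The point holds as an open risk and a mismatch between the tests and the comparative objective. The within-group contrasts are the only arm-specific tests of change, they are held to the same p<0.05 as the rest, and in this population they reflect natural recovery plus rehabilitation. They cannot show that SAEM-CS is better than control, SA or rTMS.

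With no treatment effect and 15 per arm, the misleading pattern of SAEM-CS significant and control not would arise in 25%, 15% or 5% of trials at an assumed standardised recovery of 0.5, 0.8 or 1.0, and almost never at 1.5, where nearly every arm is significant.

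This rests on equal recovery in all arms, one contrast per arm with its own error term, and Tukey being applied to the group factor. If Tukey is meant for change scores, saying so would close most of the gap. The point deserves correction because the remedy is small, but it does not undermine the design or the sample size.

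**What to change.** Amend the Data analysis section to say three things:

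- Efficacy on the FMA is judged by the group-by-time comparison of change.
- That test is followed by Tukey-adjusted between-arm contrasts of change from baseline, SAEM-CS versus each other arm, at the end of intervention and at follow-up.
- Within-arm changes are reported descriptively, as mean change with 95% CI per visit. No efficacy conclusion is drawn from one arm's change or from comparing p values across arms.

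The cost is a few sentences, slightly more analysis work, and fewer significant results to report. No patients, visits or data are added, and the sample size does not change.

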### Confidentiality and data management

Participant identification records will be kept confidential until the results of this study are published. All documents related to a clinical trial, such as case report forms (CRFs), will be recorded and labeled with participant identification codes and will not show the name of the participant. The serial number codes will be inserted in sealed, opaque envelopes, kept in a double-locked cabinet, and opened in the presence of the patient and a guardian.

All data of the participants will be recorded in Excel files by the CRC. Additionally, raw data (CRFs) will be kept in a cabinet until the end of this study.

Written informed consent will be obtained from the participants for publication of their individual details and accompanying images in this manuscript. The consent forms will be available for review by the Editor-in-Chief.

